## Abstract

**Background:**

The best reperfusion strategy for medium-sized vessel occlusion (MeVO) is not well established. Given the proven treatment effect of intra-arterial thrombolysis in patients with large vessel occlusion (LVO), we hypothesized that intra-arterial tenecteplase (TNK) could increase the recanalization rate of MeVO and thus improve clinical outcome.

**Aims:**

To explore the safety and efficacy of intra-arterial TNK in patients with MeVO.

**Sample size estimates:**

A maximum of 80 patients are required to test the superiority hypothesis, using power = 80% and *α* = 0.025 to conduct the one-sided test.

**Design:**

Rescue treatment for mEdium veSsel oCclUsion by intra-artErial TNK (RESCUE-TNK) is a pilot, randomized, open-label, blinded end point, and multicenter trial. Eligible patients including primary MeVO as detected by the first DSA examination or secondary MeVO after endovascular treatment (EVT) for LVO will be assigned into the experimental group and control group as a ratio of 1:1. The experimental group will be treated with intra-arterial TNK (0.2–0.3 mg/min, for 20–30 min) *via* a microcatheter placed proximal to the site of occlusion, and the control group will be treated with routine therapy. Both groups of patients will be given standard stroke care based on the guidelines.

**Outcome:**

The primary efficacy end point is successful recanalization of MeVO, defined as the expanded treatment in cerebral ischemia (eTICI) score 2b67-3 after the procedure, while the primary safety end point is symptomatic intracranial hemorrhage (sICH), defined as National Institutes of Health Stroke Scale score increase ≥4 caused by intracranial hemorrhage within 24 (−6/+24) hours after randomization.

**Conclusion:**

The results of RESCUE-TNK will provide evidence for the efficacy and safety of intra-arterial TNK in the recanalization of patients with MeVO.

## Introduction and rationale

Reperfusion of an occluded artery is the primary treatment goal in acute ischemic stroke (AIS) to achieve good clinical outcomes. Endovascular treatment (EVT) is recommended as the standard of care in patients presenting with acute large vessel occlusion (LVO). (1) Medium-sized vessel occlusion (MeVO), usually defined as occlusions of the M2-3, A1-3, P1-3, anterior inferior cerebellar artery (AICA), posterior inferior cerebellar artery (PICA) or superior cerebellar artery (SCA) segment, accounts for 25–40% of AIS, (2) mainly involving primary isolated MeVO or secondary embolism caused by EVT or intravenous thrombolysis (IVT). Due to a more distal site of arterial occlusion and a relatively smaller infarct size, the prognosis of MeVO stroke is generally better than LVO. However, the prognosis remains poor in many patients, (3) particularly in those with primary M2-3, A1, P1 MeVO or secondary MeVO including emboli to new territories and emboli to distal territories in the setting of EVT. (4)

In patients with disabling MeVO, treatment decision-making can be a challenge for physicians. Some studies have shown that EVT for MeVO is safe and may confer benefit, (5–7) while other studies have reported a high risk of intracranial hemorrhage (ICH). (8, 9) In addition, EVT for MeVO is restricted by many factors, including relatively greater anatomical tortuosity to reach the target site of occlusion, the need for lower-profile devices for smaller arteries, and operator skill. Among neurointerventionalists, the inclination for treating MeVO with a mechanical device is significantly greater in patients who are ineligible for IVT compared to those who are IVT eligible. (10) Thus, the treatment for MeVO in clinical practice will vary according to the patient’s eligibility for IVT, different centers, or operators. In PROACT-II (11), which demonstrated the efficacy and safety of local thrombolysis with prourokinase for LVO, intra-arterial prourokinase increased partial or complete reperfusion rates among 44 patients with isolated M2 occlusions (12). This was also confirmed in another study demonstrating greater reperfusion rates with rescue intra-arterial urokinase after failed or incomplete reperfusion with mechanical thrombectomy. (13)

As the latest generation of thrombolytic drugs, tenecteplase (TNK) has been found to be associated with higher reperfusion rates and better functional outcome than alteplase in bridging EVT patients with large vessel occlusion both in anterior and posterior circulation, (14) although this was not confirmed in the ACT trial (15). In our recent unpublished study, intra-arterial TNK (12 mg) was used during mechanical thrombectomy for large vessel occlusion patients and found the treatment did not increase the risk of cerebral hemorrhage.

In this context, we hypothesized that intra-arterial TNK could increase the recanalization rate and thus improve clinical outcomes in MeVO patients who are considered ineligible for mechanical clot retrieval. Therefore, the purpose of this study is to explore the safety and efficacy of this treatment strategy.

## Methods

### Design

Rescue treatment for mEdium veSsel oCclUsion by intra-artErial TNK (RESCUE-TNK) is a pilot, randomized, open-label, blinded end point, and multicenter study in China aiming to evaluate the safety and efficacy of intra-arterial TNK in patients presenting with MeVO. The trial flowchart is shown in Figure 1. For primary MeVO, CTA or MRA will be usually used to screen the eligibility, which will be confirmed by DSA; for secondary MeVO, DSA will be usually screened and confirmed for the eligibility.

**Figure 1 fig1:**
[figure not shown]
Trial flowchart. R, randomization; NIHSS, national institutes of health stroke scale; mRS, modified ranking scale.

### Study population

In the RESCUE-TNK trial, eligible participants are AIS patients with primary MeVO detected by the first DSA, or secondary MeVO after mechanical thrombectomy. Patients will be enrolled at approximately 20 sites in China between March 2023 and March 2025. The detailed inclusion/exclusion criteria are listed in Table 1. Specifically, intravenous thrombolysis should be administrated within 270 min according to current guidelines.

**Table 1 tab1:** Inclusion/exclusion criteria.

Inclusion criteria:
Age ≥ 18 years;
Medium vessel occlusion (MeVO), referring to M2-3 of MCA; A1-3 of ACA; P1-3 of PCA; PICA, AICA or SCA (including primary, distal embolism in the same region after thrombectomy or concurrent embolism in other regions).
Primary MeVO as detected by the first DSA examination or secondary MeVO after mechanical thrombectomy for large vessel occlusion;
MeVO causes neurological deficits in motor strength, language, vision etc.;
Endovascular mechanical thrombectomy cannot be performed as assessed by the investigator;
Absence of parenchymal hematoma on CT images performed in the angio suite.
Within 24 h from symptom onset;
Signed informed consent by patient or patient’s legally authorized representative.
Exclusion criteria:
Patients with completed infarction in the territory of the MeVO on non-contrast CT;
Patients with intracranial hemorrhage;
Coagulation disorders, tendency for systemic hemorrhagic, thrombocytopenia (<100,000/mm^3^);
Severe hepatic or renal dysfunction, increase in ALT or AST (more than 2 times of upper limit of normal value), increase in serum creatinine (more than 1.5 times of upper limit of normal value) or requiring dialysis;
After mechanical thrombectomy, severe and sustained (> 5 min) uncontrolled hypertension (systolic blood pressure over 180 mmHg or diastolic blood pressure over 105 mmHg);
Patients with contraindication or allergy to any ingredient of study medication;
Pregnancy, plan to get pregnant or active lactation;
The estimated life expectancy is less than 6 months due to other serious diseases;
Other conditions unsuitable for this clinical study as assessed by researcher.

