### Randomization and intervention

Eligible patients will be assigned into an experimental group and a control group as a 1:1 ratio by using central and computerized random sequence generation (dynamic randomization-minimization) as stratified by center. The experimental group will be treated with intra-arterial (IA) TNK *via* a microcatheter proximal to the site of the occlusion for 20 to 30 min. TNK will be temporarily stopped at 20 min from the onset of infusion, at which time recanalization status will be adjudicated by DSA. If successful recanalization is not achieved, TNK will be administered for the remaining 10 min. Different doses of intra-arterial TNK will be given based on whether intravenous thrombolysis or rescue balloon angioplasty and/or stenting is performed: (1) 0.3 mg/min IA TNK if neither treatment was given; (2) 0.25 mg/min IA TNK if either of them was given; (3) 0.2 mg/min IA TNK if both treatments were given. The control group will be treated with routine therapy. Both groups of patients will be given standard care based on the guidelines. (16, 17)

During the first 24 h, we recommend that SBP will be tightly controlled to less than 180/100 mmHg and less than 140/90 mmHg if eTICI ≥2b67 is achieved; blood glucose level will be controlled to less than 160 mg/dl.

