### Outcomes

The primary efficacy end point is proportion of patients with successful MeVO recanalization, defined as the expanded treatment in cerebral ischemia (eTICI) score 2b67-3 in the territory of the target occluded MeVO artery. (18)

The secondary efficacy end points are as follows: (1) proportion of modified Rankin Scale (mRS) 0–1 at 90 days; (2) proportion of mRS (0–2) at 90 days; (3) distribution of mRS at 90 days; (4) incidence of early neurological improvement (ENI), defined as a decrease of more than four points or reaching zero points in NIHSS score, compared with baseline at 24 (−6/+24) hours; (5) change in NIHSS compared with baseline at 24 (−6/+24) hours; (6) rate of visual recovery in patients with posterior cerebral artery occlusion at 7 days or at hospital discharge, whichever is earlier (categorized as no recovery, partial recovery and complete recovery).

The primary safety end point is the proportion of symptomatic intracranial hemorrhage (sICH) within 24 (−6/+24) hours, which is defined as an increase in the NIHSS score of ≥4 points as a result of the intracranial hemorrhage (19).

The secondary safety end points include proportion of parenchymal hematoma type 1 and 2 (PH1 and PH2) at 24 (−6/+24) hours, all serious adverse events at 24 (−6/+24) hours, all-cause death within 7 ± 2 days or during hospitalization and proportion of recurrent stroke, cardiovascular events, other vascular events and death within 90 days.

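### The only blood-pressure exclusion applies after thrombectomy, so no numeric entry limit covers primary-MeVO patients who have had none

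*Protocol article*

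**What the plan says.** The article's Study population section refers the reader to Table 1 for the detailed criteria. Table 1 admits two kinds of patient: "Primary MeVO as detected by the first DSA examination or secondary MeVO after mechanical thrombectomy for large vessel occlusion". It also requires of every patient: "Endovascular mechanical thrombectomy cannot be performed as assessed by the investigator". The Introduction describes the target population in the same way, as "MeVO patients who are considered ineligible for mechanical clot retrieval".

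The only exclusion in Table 1 that mentions blood pressure begins "After mechanical thrombectomy, severe and sustained (> 5 min) uncontrolled hypertension". It then sets the threshold at a systolic pressure above 180 mmHg or a diastolic pressure above 105 mmHg.

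Two other exclusions could bear on a severely hypertensive patient, but neither names a pressure: "Patients with contraindication or allergy to any ingredient of study medication" and "Other conditions unsuitable for this clinical study as assessed by researcher".

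Blood pressure appears once more, under Randomization and intervention. For the first 24 hours the text reads "we recommend that SBP will be tightly controlled to less than 180/100 mmHg", with a lower target of 140/90 mmHg once the vessel is successfully reopened.

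**The concern.** The opening words of the exclusion tie it to one of the two entry routes. A patient with secondary MeVO whose pressure stays above 180/105 mmHg after thrombectomy is excluded by rule. A patient with primary MeVO and the same pressure, who has had no thrombectomy, is not. Both can be randomized to an intra-arterial thrombolytic, and symptomatic intracranial hemorrhage is the primary safety end point.

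For the primary-MeVO patient, entry at that pressure depends on whether an investigator regards it as a contraindication to the drug or as a reason for unsuitability. With about 20 sites, that judgement may differ from one site to another.

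**Working it through.** No figure in the plan needs to be reproduced here. The check is a reading of all the eligibility criteria against the intervention text.

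1. **Does the exclusion reach primary MeVO?** Its trigger is a preceding thrombectomy. Table 1 requires that thrombectomy cannot be performed, and primary MeVO is identified at the first angiogram. Such a patient ordinarily has no thrombectomy before randomization, so the trigger does not occur. A failed attempt before randomization is the possible exception.

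2. **Does another criterion set a numeric limit?** No other inclusion or exclusion criterion in Table 1 gives a blood pressure. The contraindication and unsuitability exclusions apply to everyone but state no threshold.

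3. **Does the 24-hour target act as an entry limit?** The two sets of numbers compare as follows:
   - Exclusion in Table 1: systolic above 180 or diastolic above 105 mmHg, for more than 5 minutes, after thrombectomy.
   - Management target: below 180/100 mmHg, both groups, first 24 hours, worded as a recommendation.

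   The diastolic target is 105 − 100 = 5 mmHg stricter, so any patient above the exclusion limit is also above the target. The target does not decide who may be randomized.

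4. **Is treatment different for primary MeVO?** The experimental group receives intra-arterial TNK for 20 to 30 minutes whatever the type of MeVO. The infusion rate (0.2, 0.25 or 0.3 mg/min) depends on whether intravenous thrombolysis and rescue angioplasty or stenting were given. Neither the drug nor the dose rule separates primary from secondary MeVO, so the intervention text offers no reason for a narrower limit.

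5. **Are the other bleeding-related exclusions restricted in this way?** No. Existing intracranial hemorrhage, coagulation disorders and a platelet count below 100,000/mm³ exclude a patient by either route. Only the blood-pressure limit is tied to one route.

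6. **How many patients are affected?** The count would be 80 × (share with primary MeVO and no thrombectomy attempt) × (share of those with sustained pressure above 180/105 mmHg not caught by another criterion). The document gives neither share, so no figure can be put on it.

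**The case against.** The strongest reply is that the wording is narrow but the practical gap is small. The contraindication exclusion is mandatory for every patient. If the product labelling treats severe uncontrolled hypertension as a contraindication, that criterion largely closes the gap by rule. The management target covers both types of MeVO and has a stricter diastolic limit. If its 24 hours include the infusion, treating a patient above 180/105 mmHg would go against the stated advice. Guideline-based care and the safety committee's review of hemorrhagic events add further protection. A special limit just after thrombectomy, alongside general rules for everyone, can be a coherent design, and a journal article need not justify each criterion.

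Much of this stands as mitigation. Primary-MeVO patients are not unprotected, the number affected could be a handful or none, and the missing rationale is not in itself a fault.

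It does not close the gap. The labelling and the guidelines are not in the document, and Table 1 takes no pressure limit from them. The target is a recommendation about management and does not state when its 24 hours begin. Safety monitoring acts after patients have been treated. Nor is this detail left to a fuller document: the article presents Table 1 as the detailed list, and the limit is there with its numbers and duration, but with a scope that is too narrow.

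**Conclusion.** The point holds. As written, no numeric blood-pressure entry limit reaches primary-MeVO patients without a prior thrombectomy, although they can be randomized to the same thrombolytic as the patients whom the limit does cover.

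The consequence is confined to patient safety and uniform eligibility. Eligibility is settled before allocation, so the randomized comparison is not biased, and sample size, error rates and analysis are untouched. The size cannot be computed and may be small.

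The conclusion rests on reading the opening words of the exclusion literally, and on the inference that primary-MeVO patients ordinarily have had no thrombectomy at entry. It should be corrected because the correction is cheap, but it does not threaten the validity of the trial.

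**What to change.** Widen the scope of the existing exclusion and keep its numbers. Suggested wording: *uncontrolled hypertension before randomization (systolic above 180 or diastolic above 105 mmHg, lasting more than 5 minutes), including after thrombectomy where one was performed*. This covers both types of MeVO and preserves the present rule for secondary MeVO. If the limit was always meant for everyone, the change only states that intent.

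The cost is one phrase in Table 1 and the matching item on the case report form. A few primary-MeVO patients would need pressure control before randomization or would become ineligible.

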### Standard protocol approvals, registrations, and patient consents

The RESCUE-TNK trial is listed on www.clinicaltrial.gov (NCT05657470). The protocol and data collection of the trial will/have been approved by the ethics committee of the General Hospital of Northern Theater Command and all participating sites. All patients or their representatives will provide written informed consent before inclusion into the trial.

### Randomization and intervention

Eligible patients will be assigned into an experimental group and a control group as a 1:1 ratio by using central and computerized random sequence generation (dynamic randomization-minimization) as stratified by center. The experimental group will be treated with intra-arterial (IA) TNK *via* a microcatheter proximal to the site of the occlusion for 20 to 30 min. TNK will be temporarily stopped at 20 min from the onset of infusion, at which time recanalization status will be adjudicated by DSA. If successful recanalization is not achieved, TNK will be administered for the remaining 10 min. Different doses of intra-arterial TNK will be given based on whether intravenous thrombolysis or rescue balloon angioplasty and/or stenting is performed: (1) 0.3 mg/min IA TNK if neither treatment was given; (2) 0.25 mg/min IA TNK if either of them was given; (3) 0.2 mg/min IA TNK if both treatments were given. The control group will be treated with routine therapy. Both groups of patients will be given standard care based on the guidelines. (16, 17)

During the first 24 h, we recommend that SBP will be tightly controlled to less than 180/100 mmHg and less than 140/90 mmHg if eTICI ≥2b67 is achieved; blood glucose level will be controlled to less than 160 mg/dl.

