### Sample size determination

Subgroup analysis of PROACTII found that the reperfusion rate of intra-arterial thrombolysis for M2 occlusion was 53.6%, while that of the control group was 16.7%, (12) with a difference of 36.9%. Accordingly, we estimate that the proportion of recanalization of MeVO in the control group in this study will be 20%, while the proportion in the experimental group is conservatively estimated to be 50%, with a 30% increase. Using a power of 80% and *α* of 0.025 to carry out the one-side test, the calculated sample size is 72. In consideration of the 10% lost to follow-up, the total sample size is 80. Therefore, this study will include 80 patients, with 40 patients in each group.

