### Statistical analysis

An intention-to-treat (ITT) analysis will be used to analyze the therapeutic effects of the two groups and all data will be analyzed with SPSS 20.0 Software. The mean ± standard deviation (SD) will be used if the data are normally distributed; the median and interquartile range (IQR) will be used if the data are not normally distributed. Differences in the proportion of successful recanalization of MeVO (eTICI score 2b67-3 for the target vessel), mRS (0–1) at 90 days, mRS (0–2) at 90 days, and ENI will be compared using binary logistic regression. The distribution of the mRS at 90 days between the two groups will be compared using ordinal logistic regression. Time-to-events of stroke recurrence and other vascular events will be compared using Cox regression. The change in NIHSS score within 48 h between the two groups will be compared using a general linear model. All statistical tests are 2-sided, using *α* = 0.05 and *p* < 0.05 as considered statistically significant.

The subgroup for primary endpoint will be performed by age, sex, different doses of TNK, type of MeVO, NIHSS score at presentation, time from onset to randomization, whether intravenous thrombolysis, stroke territory, and stroke etiology.

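### Allocation is balanced by centre but the primary logistic model names no centre term; run as written, the test is mildly conservative and forgoes up to about 3 points of power

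*Protocol article*

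**What the plan says.** All references are to the protocol article.

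- Randomization and intervention: patients are "assigned into an experimental group and a control group as a 1:1 ratio", by a central computerized minimization procedure "as stratified by center". Centre is the only factor named.
- Study population: "Patients will be enrolled at approximately 20 sites in China".
- Sample size determination: 80 patients, 40 per arm, with recanalization assumed to be 20% under control and 50% under treatment.
- Outcomes: "The primary efficacy end point is proportion of patients with successful MeVO recanalization", a binary end point.
- Statistical analysis: this end point and three other binary ones "will be compared using binary logistic regression". No covariates are listed. The model is not called unadjusted, and centre is neither included nor excluded.

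**The concern.** Balancing allocation on a factor removes the between-level part of the variation from the treatment comparison. A model that omits the factor still counts that variation in its standard error. If recanalization rates differ by centre, the unadjusted Wald test then rejects less often than its nominal 5%, and some of the precision bought by the balancing is not used.

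Centre differences are plausible here. The Introduction says that treatment of these occlusions varies with centre and operator, the Discussion adds devices and operator skill, and entry depends on the local investigator judging that thrombectomy cannot be done. At stake is a small amount of power in an 80-patient trial whose design power is only a little above 80%.

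**Working it through.** **Inputs from the article.** Rates 20% and 50%; one-sided 0.025, which has the same critical value as the two-sided 0.05 under Statistical analysis; power 80%; 10% loss; 80 patients; about 20 sites. That is 80/20 = 4 patients per centre, or 2 per arm per centre.

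**Reproducing the sample size.** Unpooled formula: n per arm = (1.960 + 0.842)² × (0.2×0.8 + 0.5×0.5) / 0.30² = 7.849 × 0.41 / 0.09 = 35.76, so 36 per arm and 72 in total. Then 72/0.9 = 80. Both stated figures reproduce.

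**Margin without any centre effect.** With the pooled null variance (mean rate 0.35), power at 40 per arm is Φ[(0.30 − 1.96×√(0.455/40)) / √(0.41/40)] = Φ(0.899) = 81.6%. At 36 per arm it is 77.2%. Loss should be small for an end point read at the end of the procedure, but there is little to spare.

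**Assumption.** The article gives no between-centre variation. It is varied here as a random centre intercept with standard deviation s on the logit scale, or as the latent intraclass correlation ICC = s²/(s² + π²/3). ICC 0.05, 0.10 and 0.20 correspond to s = 0.42, 0.60 and 0.91.

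**Unadjusted model v random intercept.** Both simulations use 80 patients in 20 centres of uneven size. A alternates allocation within centre, holds marginal success at 20% v 50% (null: 35% in both arms) and has about 3,100 to 4,700 runs per scenario. B has 2,000 runs per scenario. Each cell is unadjusted v random intercept.

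| Latent ICC | Type I, A | Type I, B | Power, A | Power, B |
|---|---|---|---|---|
| 0 | not run | 4.9% v 4.8% | 82.2% v 82.5% | 81.6% v 81.7% |
| 0.05 | 4.3% v 4.8% | 3.8% v 4.0% | 82.1% v 83.1% | 81.6% v 81.9% |
| 0.10 | 4.5% v 5.3% | 4.1% v 4.6% | 82.3% v 84.0% | 81.5% v 82.6% |
| 0.20 | 3.5% v 4.4% | 3.7% v 4.4% | 83.6% v 86.5% | 83.5% v 85.5% |

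Power differences at ICC 0.05, 0.10 and 0.20 are 1.0, 1.7 and 2.9 points in A, and 0.3, 1.1 and 2.0 points in B. The Monte Carlo standard error of a type I figure near 5% is √(0.05×0.95/2000) = 0.5 points in B and 0.3 to 0.4 in A, so single cells should not be over-read.

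**Is balancing the cause?** A third simulation used 20 centres of equal probability and a 0.9 biased coin within centre. Unadjusted type I error was 4.7%, 4.3%, 3.4% and 2.4% at s = 0, 0.5, 1.0 and 1.5. Under simple randomization at s = 1.0 it was 4.8%. The fall therefore comes from balancing on centre and then omitting it. The 4.7% at s = 0 shows that a small part is ordinary small-sample Wald behaviour.

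**Other ways of using centre** (third simulation).

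- About 20 fixed indicators: type I error 9.1%, 7.1% and 6.5% at s = 0, 0.5 and 1.0. The median log odds ratio was 1.87 at s = 0 against a true ln 4 = 1.39.
- Centre-stratified Mantel-Haenszel test: type I error 4.7% to 5.0%. Power was 79.1%, 80.9%, 85.1% and 89.5% at s = 0, 0.5, 1.0 and 1.5, against 81.5%, 82.2%, 83.0% and 84.1% unadjusted. It is worse at low heterogeneity and better only when centres differ markedly.

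**The case against.** **The article is silent; it does not exclude centre.** This stands. A reader might infer that the primary model ignores centre, or that the analysis contradicts the randomization. The text supports neither. The article lists no covariates for any model, it condenses a fuller protocol, and a statistical analysis plan that is not shown may already include centre. Likewise, centre is the only factor named, which is less than the only factor used. The point therefore concerns the model if it is run as written.

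**No harm is shown.** Largely right. Unadjusted power is at least 81.5% in every scenario above and does not fall as centre variation grows. The loss is relative to a better-matched model, and the error lies on the safe side.

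**The gain is mostly test size.** By normal approximation, the type I differences in A alone would give about 1.2, 1.8 and 2.2 points of power, against 1.0, 1.7 and 2.9 observed. That is a fair description, but recovering the nominal size is what matching the model to the allocation should do.

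**The random intercept may not be free when centres do not differ.** In the third simulation its likelihood ratio test had type I error of 5.9% at s = 0 (1,500 runs, standard error about 0.6 points). Its 84.2% power there, against 81.5% unadjusted, cannot be real precision. Simulation B shows 4.8% v 4.9% and 81.7% v 81.6% at ICC 0. The supportable statement is no detectable cost, which is weaker than no cost.

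**A stratified test can lose power.** True of Mantel-Haenszel at s of 0 to 0.5, by about 1 to 2 points, but that is not the change proposed.

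**The estimand shifts.** This stands. A random-intercept odds ratio is conditional on centre. With marginal rates fixed at 20% and 50%, the log odds ratio is 1.39 with no centre variation and 1.46 at s = 0.5, an odds ratio of 4.0 against 4.3.

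**Conclusion.** The point holds as a minor improvement. If the primary logistic model is run without centre, it is mildly conservative when success rates differ by centre: type I error is about 3.5% to 4.5% at assumed latent ICCs of 0.05 to 0.20, and about 0.3 to 3 points of power are forgone relative to a random-intercept model. With no centre variation nothing is gained or detectably lost.

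A reader might go further and conclude that the primary test is invalid or the trial underpowered because of this. Neither follows: the test does not become anti-conservative in any scenario examined, and unadjusted power stays above 80% with all 80 patients.

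The direction follows from balancing on a prognostic factor and omitting it. The size rests on the assumed ICC, on about 20 centres of about 4 patients, on close within-centre balance, and on the planned 20% and 50%. At ICC 0.05 or below the gain is about a point or less, close to simulation noise.

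**What to change.** Add one sentence to Statistical analysis: the primary binary model is a mixed logistic model with treatment as a fixed effect and a random intercept for centre; if it does not converge, the unadjusted logistic model is used. State that centre will not be entered as about 20 fixed indicators. Report the marginal risk difference beside the odds ratio, because the latter is conditional on centre and the sample size was set on marginal rates.

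The cost is that wording. Centre is already recorded and no patients are added. Three small downsides should be accepted openly: possible non-convergence, which the fallback covers although the operating characteristics of the two-step rule were not simulated; the change in meaning of the odds ratio; and the need to confirm that the named software, SPSS 20.0, can fit the model. Extending the random intercept to the ordinal and other secondary end points is optional and was not simulated. If the full protocol or analysis plan already specifies how centre enters, check only that it does not use fixed indicators.
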